#### Pressure algometry of pain threshold

A pressure algometer (digital algometer, model DDK 20, manufactured by Kratos Ltd., Cotia, Sao Paulo, Brazil) is a device that assesses the pain threshold. This device consists of a round rubber disk (1 cm^2^) attached to a pressure (force) gauge. The gauge displays values in kilograms. Because the surface of the rubber tip is 1 cm^2^, the readings are expressed in kilogram per square centimeter (kg/cm^2^). The range of the algometer is 0 to 10 kg and records in 0.1 kg divisions. At one end of the device, perpendicular pressure is applied to the surface of the skin and recorded using a manometer. The algometry of the pain threshold on the tender points will be performed based on the fibromyalgia classification criteria of the ACR, following the procedures described below:

•The patient will be asked to sit in a chair with feet supported on the ground and hands supported on the lap;

•The tender points will be marked with a skin marking pen and evaluated bilaterally in the following order: occipital, anterior lower cervical, trapezius, supraspinatus, second costochondral joint, lateral epicondyle and medial edge of the knee;

•The patient will be instructed to remain in an orthostatic position and the tender points of the gluteus and greater trochanter will be marked with the pen, bilaterally;

•During the assessment of the pain threshold on the tender points, perpendicular pressure will be applied to the surface of the skin and increased gradually in increments of 0.1 kg until the patient reports feeling pain;

•Positive results will be those below 2.6 kg/cm^2^, which is equivalent to the 4.0 kg/cm^2^ described in studies by Wolfe *et al*. [21].

#### Fibromyalgia Impact Questionnaire (FIQ)

The version of the FIQ translated into Portuguese and validated by Marques (2006) will be used. The FIQ is a quality of life assessment tool specific to fibromyalgia. The questionnaire has items addressing functional capacity, professional situation, psychological disorders and symptoms, for which higher scores denote a greater impact from fibromyalgia on quality of life.

#### Medical Outcomes Study 36-item Short-Form Health Survey (SF-36)

The version of the SF-36 translated into Portuguese and validated by Ciconelli *et al*. [22] will be used. This is a generic quality of life assessment tool consisting of 36 items distributed among eight components: functional capacity (10 items), physical aspects (4 items), pain (2 items), general health state (5 items), vitality (4 items), social aspects (2 items), emotional aspects (3 items) and mental health (5 items) as well as 1 item soliciting a comparative assessment of current health status with health status one year earlier. Each component ranges from 0 to 100 points, with higher scores denoting a better quality of life.

#### McGill Pain Questionnaire

The McGill Pain Questionnaire (MPQ) adapted to the Portuguese language will be used [23]. The questionnaire consists of a list of 78 pain descriptors organized into 4 major categories (sensory, affective, evaluative, and miscellaneous) and 20 subcategories, each made up of at least 2 and up to 6 words, to which intensity values are assigned. To calculate Pain Rating Index (PRI) the descriptors of the third category, which characterizes pain, will be used. Present Pain Intensity (PPI) will be evaluated using a verbal scale of pain (0 - no pain, 10 - very strong pain).

As some patients may have difficulty reading and understanding the instructions of the questionnaires (McGill Pain Questionnaire, SF-36 and FIQ), the reading will be performed together with the researchers.

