**Methods/design:**

One hundred and twenty patients with fibromyalgia will be treated at the Integrated Health Center and the Sleep Laboratory of the Post Graduate Program in Rehabilitation Sciences of the Nove de Julho University located in the city of Sao Paulo, Brazil. After fulfilling the eligibility criteria, a clinical evaluation and assessments of pain and sleep quality will be carried out and self-administered quality of life questionnaires will be applied. The 120 volunteers will be randomly allocated to an intervention group (LLLT, n = 60) or control group (CLLLT, n = 60). Patients from both groups will be treated three times per week for four weeks, totaling twelve sessions. However, only the LLLT group will receive an energy dose of 6 J per tender point. A standardized 50-minute exercise program will be performed after the laser application. The patients will be evaluated regarding the primary outcome (pain) using the following instruments: visual analog scale, McGill Pain Questionnaire and pressure algometry. The secondary outcome (quality of life and sleep) will be assessed with the following instruments: Medical Outcomes Study 36-item Short-Form Health Survey, Fibromyalgia Impact Questionnaire, Berlin Questionnaire, Epworth Sleepiness Scale and polysomnography. ANOVA test with repeated measurements for the time factor will be performed to test between-groups differences (followed by the Tukey-Kramer post hoc test), and a paired *t* test will be performed to test within-group differences. The level of significance for the statistical analysis will be set at 5% (*P* ≤0.05).

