### Evaluation of results

The intention-to-treat analysis will be followed. The patients will be evaluated with regard to the primary outcome (pain) using the visual analog scale for pain, the McGill Pain Questionnaire and pressure algometry. The secondary outcome (quality of life) will be assessed using the SF-36 and FIQ. The use of medication will be controlled throughout the study. The data on the use of analgesics and daily dosage of adjuvant therapy, such as antidepressants and muscle relaxers, will be recorded and tabulated.

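### The scoring rule for the McGill Pain Rating Index, taken literally, uses only the evaluative descriptors; if something else was meant, the sentence is still wrong as written

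*Protocol article*

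**What the plan says.** All of the scoring text is in the protocol article, section McGill Pain Questionnaire.

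- Content: "The questionnaire consists of a list of 78 pain descriptors". These are "organized into 4 major categories (sensory, affective, evaluative, and miscellaneous) and 20 subcategories". Each subcategory holds two to six words, and the words carry intensity values.
- Rule for the PRI: "To calculate Pain Rating Index (PRI) the descriptors of the third category, which characterizes pain, will be used".
- The only other score named: "Present Pain Intensity (PPI) will be evaluated using a verbal scale of pain (0 - no pain, 10 - very strong pain".

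The role of the questionnaire is given twice. Evaluation of results assesses the "primary outcome (pain) using the visual analog scale for pain, the McGill Pain Questionnaire and pressure algometry". The abstract (Methods/design) names the same three instruments for pain.

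**The concern.** The section sets out four categories in a fixed order and then, in its next use of that word, builds the PRI from the third. An analyst who has only this text would take the evaluative descriptors and stop there. No other sentence brings the sensory, affective or miscellaneous descriptors into the PRI or any other score.

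This is a rule that the article states, so it is not a detail left to a later plan. A later analysis plan that scored every descriptor would contradict the published rule.

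Two things are at stake. First, a result could be reported as the PRI with three of the four categories outside it. Second, two analysts could compute different PRIs from the same answers, each with a reading of the sentence to support it. For a score from a primary instrument, that leaves room to choose after the results are known.

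**Working it through.** The document gives no figure to reproduce on this point. The check is one of reading, followed by a look at whether the size can be worked out.

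**1. The ordinal against the list.** The order is (1) sensory, (2) affective, (3) evaluative, (4) miscellaneous. The PRI uses the third, which is evaluative. Categories left out: 4 − 1 = 3, namely sensory, affective and miscellaneous.

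**2. Is there a repair elsewhere?** The Present Pain Intensity is a 0 to 10 verbal scale and uses no descriptors. The abstract, Evaluation of results and Statistical analysis give no McGill scoring rule. Nothing brings the other three categories back in.

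**3. Does the clause about characterizing pain settle the meaning?** All 78 entries are described as pain descriptors, so the clause does not separate evaluative from the other three. It would fit a part of the form that holds the whole descriptor list. Against that, the section speaks only of categories and subcategories, mentions no numbered parts, and has just used the word category for the four groups.

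| Reading | What enters the PRI | Is the sentence right as written? |
|---|---|---|
| Literal: third of the four listed categories | Evaluative descriptors only | It can be followed, but omits three of four categories |
| Intended: a section of the adapted form | Possibly all 78 descriptors | No: it names a category where a section was meant |

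**4. Can a loss be calculated?** That would need the number of subcategories in the evaluative category, their correlation, and an effect size and standard deviation for the PRI. The document gives none of these. It limits the number of evaluative subcategories only to between 1 and 17: there are 20 in all, and if each of the other three categories has at least one, 20 − 3 = 17.

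An illustration shows how far the answer depends on assumptions. Suppose a correlation of r = 0.3 between any two subcategories, the same treatment effect in each, and 80% power on the full score (two-sided 5%, 45 per arm).

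- Reliability of a sum of k subcategories (Spearman-Brown): kr / (1 + (k − 1)r). For k = 20: 6.0 / 6.7 = 0.896.
- Effect relative to the full score: √(reliability for k / reliability for 20).
- Power: from the noncentral t distribution with 88 degrees of freedom.

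| k | Reliability | Relative effect | Power |
|---|---|---|---|
| 17 | 5.1 / 5.8 = 0.879 | 0.991 | 79% |
| 5 | 1.5 / 2.2 = 0.682 | 0.873 | 69% |
| 3 | 0.9 / 1.6 = 0.562 | 0.793 | 60% |
| 1 | 0.3 / 1.0 = 0.300 | 0.579 | 37% |

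With r between 0.2 and 0.5 the power is 63 to 75% for k = 5, 52 to 70% for k = 3 and 28 to 53% for k = 1. Over the values of k that the document allows, the result runs from almost no loss to a large one. These figures describe the assumptions and are not an estimate for this trial.

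**The case against.** The strongest reply is that the sentence is a slip of wording and nothing was meant to be left out. The word *only* is not in the text, and the clause about characterizing pain does not point to the evaluative group. The form is an adapted Portuguese version, and its layout and numbering are not shown. A reader might infer that the investigators decided to discard the sensory and affective descriptors. The document does not support that as settled intent, and this part of the reply stands. It does not save the sentence, which under the milder reading directs the analyst to the wrong thing.

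A second reply is that the article defines no standard PRI, so a one-category score cannot be called wrong against it. That is fair. The case for scoring all four categories is that the section describes them as one instrument, with intensity values on its words, and gives no reason for using one group. It is a recommendation and not a rule found in the text.

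Third, the reach is limited. The PRI is one of two scores from one of three pain instruments. The visual analog scale, algometry and the Present Pain Intensity are untouched, and the results anticipated in the Discussion name the first two and no McGill score. This stands, and it limits the weight of the point.

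Fourth, a condensed article may leave questionnaire scoring to the full protocol. That would answer a complaint of missing detail. Here a rule is stated, so it does not apply.

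**Conclusion.** The point holds in this form. The article fixes the PRI by reference to a third category; in its own order that is the evaluative one, and a literal analyst would omit three of the four categories from a score belonging to a primary pain instrument. If a section of the adapted form was meant, the sentence is still wrong as written. Nothing elsewhere in the article corrects it.

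The conclusion rests only on the order of the list and the wording of the rule. It needs no assumption about correlations or category sizes.

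A reader might go on to infer that the trial loses power, for example from 80% to 69%, 60% or 37%. The document does not support this. The correlation, the number of evaluative subcategories, the starting power and the equal effect across subcategories are all assumed. If the effect differs between categories, a single category could be more or less sensitive than the total, so even the direction is open. The article's only sample-size calculation (Composition of sample) is for the Fibromyalgia Impact Questionnaire, one-sided at 95% power, and has no bearing on this score.

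The correction should be made, because the score serves the primary outcome and the remedy is small.

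**What to change.** Replace the sentence on the PRI with wording such as: *The PRI is computed from the intensity values of the chosen descriptors in all four categories (20 subcategories). The sums for the separate categories are reported as supportive.*

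If a particular section of the adapted form was meant, name that section and list its subcategories, so that only one PRI can be computed from a completed form. The investigators should check the wording against the scoring instructions of the version in use.

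Trial status says that patients are being recruited, and Specifications (Low-level laser therapy) says that the active and placebo application points are identified only when data acquisition ends. The correction should be dated and recorded before then.

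The cost is one sentence. All 78 descriptors are already in the questionnaire, so no further data and no change to the visits are needed.

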#### Sleep assessment

The sleep studies will be carried out at the Sleep Laboratory of the Post Graduate Program in Rehabilitation Sciences (UNINOVE) through complete nocturnal standard level I polysomnography using the Somnologica Studio (Embla A10 version 3.1.2, Medcare Flaga, Hs. Medical Devices, Reykjavik, Iceland), composed of 16 channels for the monitoring of electroencephalogram, electrooculogram, electromyography of the submentum and tibialis anterior muscles and electrocardiogram, including channels for digital oximetry, nasal pressure (canulla), pressure transducer, respiratory movements (Xtrace thoracic and abdominal straps) and body position. The assessments will be performed manually by a specialized reader following the guidelines of the American Academy of Sleep Medicine [24], and the criteria of the Brazilian Sleep Society and the report of the results will be drafted by a specialist in sleep medicine. The Berlin Questionnaire will be administered also. This 10-item patient history questionnaire has recognized efficacy in differentiating individuals with a greater risk of sleep apnea. Moreover, the Epworth Sleepiness Scale (Johns, 1991) [25] will be employed for the assessment of excessive daytime sleepiness.

Regarding the performance of the examinations and procedures during the sleep study, the patients will be instructed to remain as relaxed as possible and sleep naturally as if at home. All signals will be recorded continuously throughout the entire sleep period of each subject.

#### Educative session

The educative session will be individual and carried out following the initial evaluation. The subject will be informed with regard to the nature of fibromyalgia, symptoms, treatment (stressing the importance of exercise) and consequences for activities of daily living. Some exercise strategies will be taught, such as extra body weight loading and adequate positions for the performance of activities of daily living and practice (work). A basic exercise program will then be taught, composed of 11 exercises for stretching the gluteus, paravertebral, hamstrings, pectoral, scalene, intercostals and trapezius muscles. The patients will receive a chart with all the information on fibromyalgia as well as illustrations and descriptions of the exercises to perform. The chart will be furnished to all patients in order to increase compliance with the at-home exercise program.

### Low-level laser therapy

#### Specifications

The Twin Laser (MM Optics Ltda., São Carlos, São Paulo, Brazil) will be employed, the active medium of which is made up of a Gallium-Aluminum-Arsenide semiconductor diode, with emission in the 780 nm near infrared wavelength (invisible) and variable power values in the continuous emission mode. The display provides the doses according to the power and application time. The laser will undergo verification of functioning, energy source, points of application and measurement of power.

To provide the ‘blinding’ of the study, the laser equipment has two identical application points furnished by the manufacturer - one active and the other a placebo (that does not emit energy); both have a sound device and guide light. The points will be named A and B by a researcher who will not participate in the treatment or evaluations. The researcher performing the applications and the evaluators will be unaware of which points received the effective dose and which received the placebo. The patients will also not have access to information regarding to which group they belong. The points will be identified only at the end of the data acquisition phase.

#### Application of laser

Both groups will receive three laser applications per week for four weeks, totaling twelve sessions. The applications will be performed in spot form with direct contact between the laser probe and the skin. However, only the patients in the effective radiation group with receive an energy dose of 6 J per point. The application points will be performed at the tender points identified prior to each session.

### Exercises

Both groups (LLLT and control) will undergo a 50-mintue exercise program following the application of the laser or placebo, which will consist of 10 minutes of warm up and stretching, 30 minutes of aerobic exercise on a treadmill and 10 minutes of relaxation and stretching, three times a week throughout the four weeks of the study.

### Evaluation of results

The intention-to-treat analysis will be followed. The patients will be evaluated with regard to the primary outcome (pain) using the visual analog scale for pain, the McGill Pain Questionnaire and pressure algometry. The secondary outcome (quality of life) will be assessed using the SF-36 and FIQ. The use of medication will be controlled throughout the study. The data on the use of analgesics and daily dosage of adjuvant therapy, such as antidepressants and muscle relaxers, will be recorded and tabulated.

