### Composition of sample

The required sample size was determined for the primary outcome variable, that is, overall score of the Fibromyalgia Impact Questionnaire (FIQ). According to Bennett *et al*. [20], a clinically relevant change is a 15 to 20% reduction in the total FIQ score (which is equal to an approximate 10 to 15 points reduction). Assuming a unilateral alternative (that is, the intervention reduces the impact of fibromyalgia), we can detect differences of at least 15% with a power of 95% and α of 0.05 with two groups (intervention and usual control group) of 45 participants, with a mean in the FIQ of approximately 70 and a standard deviation of approximately 20 points. Assuming a maximum loss of follow-up of 30%, we will recruit a total of 60 women with fibromyalgia for each group. We will recruit a total of 120 women with fibromyalgia (that is, one LLLT intervention group and control group of 60 persons each).

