### Exclusion criteria

Patients with the following will be excluded from the study:

•Psychiatric disorders, history of drug abuse or other behavior that requires psychiatric medication intervention;

•Development of situations beyond clinical control that do not allow participation in aerobic training activities, exertion or group activities;

•Severe physical disability;

•Co-morbid condition (irritable bowel syndrome, intestinal cystitis, and others);

•Uncontrolled endocrine disorders;

•Although there is no description of serious complications in individuals submitted to LLLT, those with a history of epilepsy, seizures, heart disease, arrhythmia, pacemaker, undiagnosed pain, pregnancy and malignant tumors will be excluded from the study.

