### Composition of groups and randomization

After the initial evaluation, the 120 volunteers will be randomly allocated to an intervention group (LLLT; n = 60) or control group (CLLLT; n = 60). Randomization numbers will be created using a randomization table at a central office, where a series of sealed, opaque, numbered envelopes will be used to ensure confidentiality. Each envelope will contain a card indicating the group in which the patient will participate. After fulfilling the eligibility criteria, a clinical evaluation and assessments of pain and sleep quality will be carried out and self-administered quality of life questionnaires will be applied (Fibromyalgia Impact Questionnaire, Medical Outcomes Study 36-item Short-Form Health Survey and McGill Pain Questionnaire). After the volunteer signs the statement of informed consent, she will randomly select one of the envelopes. This study received approval from the UNINOVE Human Research Ethics Committee (protocol number 474921). Additionally, the study is registered with the World Health Organization Universal Trial Number (UTN) U1111-1125-5007 and the Brazilian Registry of Clinical Trials (number - RBR-42gkzt).

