## Experimental protocol

### Evaluation and educative session

The evaluations will occur prior to and at the end of the therapeutic program by a researcher with no knowledge regarding the type of treatment to which the subjects will be submitted. All subjects in both groups will be submitted to the same evaluation protocol, which will include the aspects listed below.

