### Statistical analysis

ANOVA test with repeated measurements for the time factor will be performed to test between-groups differences (followed by the Tukey-Kramer post hoc test), and a paired *t* test will be performed to test within-group differences. The level of significance for the statistical analysis will be set at 5% (*P* ≤0.05).

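### The named two-visit ANOVA and paired t test use only patients with both evaluations unless missing end values are handled, so they do not by themselves deliver the promised intention-to-treat analysis

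*Protocol article*

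**What the plan says.** Five statements in the protocol article bear on this point.

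- **Principle** (Evaluation of results): "The intention-to-treat analysis will be followed".
- **Tests** (Statistical analysis): "ANOVA test with repeated measurements for the time factor will be performed to test between-groups differences", with Tukey-Kramer comparisons to follow. A paired t "test will be performed to test within-group differences".
- **Visits** (Evaluation and educative session): "The evaluations will occur prior to and at the end of the therapeutic program". No intermediate outcome visit is described.
- **Numbers** (Composition of groups and randomization; Composition of sample): "the 120 volunteers will be randomly allocated to an intervention group (LLLT; n = 60) or control group (CLLLT; n = 60"), and "Assuming a maximum loss of follow-up of 30%, we will recruit a total of 60 women with fibromyalgia for each group".
- **Exclusion** (Exclusion criteria): one bullet reads "Development of situations beyond clinical control that do not allow participation in aerobic training activities, exertion or group activities". Composition of groups and randomization places the check of eligibility ahead of the baseline assessments and the envelope draw.

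The article does not say what happens in the analysis to a randomised patient who has no end evaluation.

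**The concern.** Intention-to-treat concerns who is compared: everyone randomised, in the arm drawn. The tests named in the next section settle, by their form, who can be compared: patients with both a baseline and an end value. The two sets coincide only if nobody is lost, or if missing end values are dealt with first. The plan itself allows for sizeable loss.

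Two things are at stake. The first is that the balance created by randomisation belongs to all 120 patients, not to those who finish. Each of the twelve sessions includes 50 minutes of exercise, so finishing may plausibly be related to pain, which Evaluation of results makes the primary outcome. The second is the assumption about missing values. A change-score comparison of completers needs a stronger one than a baseline-adjusted analysis that uses baseline data already collected.

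The exclusion bullet adds an ambiguity. Its opening word could describe something arising after entry. Applied after allocation and carried into the analysis, it would take out patients because they could not exercise.

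**Working it through.** **Inputs.** 120 randomised, 60 per arm (Composition of groups and randomization). Two evaluations (Evaluation and educative session). Maximum loss 30%, 45 evaluable per arm, FIQ mean about 70, SD about 20, difference at least 15%, one-sided alpha 0.05, power 95% (Composition of sample).

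**1. The plan's own figures.** Per arm, n = 2 × SD² × (z₀.₉₅ + z₀.₉₅)² / δ², with z₀.₉₅ = 1.645.

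- δ = 15% of 70 = 10.5: n = 2 × 400 × 10.82 / 110.25 = 78.5, so 79.
- δ = 20% of 70 = 14: n = 2 × 400 × 10.82 / 196 = 44.2, so 45.
- Loss allowance: 45 / 0.70 = 64.3, so 65; 45 × 1.30 = 58.5, so 59, close to the stated 60.

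The 45 is reproduced at 20%, not at the stated 15%, and 60 per arm less 30% is 42, not 45. Those are separate matters. Only the 60 per arm and the 30% are carried forward here.

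**2. Patients with no end value.**

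| Loss | Without end value (of 120) | With both values | Per arm, if equal |
|---|---|---|---|
| 10% | 12 | 108 | 54 |
| 20% | 24 | 96 | 48 |
| 25% | 30 | 90 | 45 |
| 30% (plan's maximum) | 0.30 × 120 = 36 | 84 | 42 |

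**3. What the named tests use.** Let D = end value − baseline value. With two visits, the group-by-time F of the repeated-measures ANOVA is the square of the two-sample t on D:

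F = [(mean D, LLLT − mean D, control) / (s_D × √(1/n₁ + 1/n₀))]².

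On a simulated data set of 120 patients with 18 end values missing per arm, F = 5.23 and t² = 5.23 in the 84 completers. A patient with a baseline value only has no D and does not enter. The paired t, mean D / (s_D / √n), has the same limit.

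**4. Precision.** One-sided power on the plan's FIQ inputs (normal approximation):

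| Patients with end values | δ = 10.5 | δ = 14 |
|---|---|---|
| 42 per arm | 77.7% | 94.1% |
| 60 per arm | 89.1% | 98.6% |

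The second row needs observed end values. Modelling or imputation from baseline alone recovers little of that gap, because a baseline-only patient says little about the end-visit contrast.

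**5. The missingness assumption.** Suppose the end value has slope β on baseline, the same in both arms, and true effect τ. If drop-out depends on arm and baseline only, the completers' change contrast is

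τ + (β − 1) × (mean baseline of LLLT completers − mean baseline of control completers).

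The second term vanishes only if β = 1 or the completers' baselines are balanced. A baseline-adjusted analysis removes it. The documents do not give β, so no size is attached. If drop-out depends on the unseen end value itself, neither analysis is safe without a sensitivity analysis.

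**6. The exclusion bullet.** It stands in a list of entry criteria, and eligibility is applied before the envelope is drawn. This favours reading it as a screening rule, but its wording leaves the other reading open. Nothing states that it does not touch patients already randomised.

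**The case against.** The strongest reply is that this is a request for a missing-data rule, which a condensed article may leave to a fuller protocol or analysis plan. No section says that patients without an end visit are removed, that the analysis is complete-case, or that values will not be imputed. ANOVA and paired t tests can be run on imputed data, so principle and tests can be reconciled. Recruiting extra patients for expected loss is routine and does not show that a completer population is intended. All of this stands. The absence of an imputation rule is therefore not the point. The point is that the method the article does choose is a change-score analysis that, as named, falls short of the principle it states.

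A reader might infer three stronger things that the documents do not support.

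- **That 30% of patients will leave the analysis.** The 30% is a planning ceiling for loss to follow-up, not a product of the tests.
- **That the exclusion bullet removes patients after randomisation.** It is ambiguous, and the order of procedures points to screening.
- **That the treatment effect is inflated by a known amount.** Both arms do the same exercise, and patients and staff are blinded with a matching sham probe, so intolerance of exercise is shared. The documents give no reason to expect drop-out to differ by arm. As pure illustration, assume 30% loss and LLLT drop-outs who are worse than LLLT completers by 10 FIQ points (0.5 SD), with no such gap among controls. The overstatement is 0.30 × 10 = 3 points, or 3 / 10.5 = 29% of the 15% target. With the same gap in both arms it is zero. The figure only restates its assumptions, and it concerns FIQ, which Evaluation of results lists as secondary.

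It is also fair to say that a mixed model or imputation under missing at random would not remove that illustrated bias. Hence the sensitivity analysis in the fix.

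**Conclusion.** The concern holds in limited form. The tests as named draw only on patients with both evaluations unless missing end values are handled, so they do not by themselves give the intention-to-treat comparison. At the plan's maximum loss this affects up to 36 of 120 randomised patients, leaving 84. That count rests on the 30% ceiling being reached and on no imputation or likelihood model being applied. The 42 per arm also assumes equal loss in the two arms.

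The article does not contradict itself outright, and no size or direction of bias can be derived from it. The case for change is that the named analysis needs a stronger missingness assumption than an alternative that uses data already collected. It is worth correcting before analysis, but it does not undermine the design.

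**What to change.** 1. **Primary comparison.** For each pain outcome, compare all randomised patients in their allocated arm with adjustment for baseline. Use either a likelihood-based repeated-measures model with baseline and end values as responses, a common baseline mean and group-by-time, or ANCOVA after multiple imputation done separately by arm. Name one of these in advance.
2. **Within-group tests.** Keep the paired t tests as descriptive only.
3. **Sensitivity analysis.** Add one delta-adjusted analysis that shifts the unobserved end values in each arm over a stated range. The main model assumes missing at random and would not correct for worse unseen outcomes among one arm's drop-outs.
4. **Exclusion bullet.** Reconcile it with Composition of groups and randomization and with Evaluation of results, by stating that it does not remove randomised patients from the analysis.
5. **End evaluation.** State that patients who stop attending sessions are still invited to the end evaluation already planned. Observed values protect power and validity better than any model.

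The cost is revised wording, modest extra programming and an explicit missing-at-random assumption. No additional patients or new measurements are needed. Recruitment was under way when the article was submitted, so the change should be dated and fixed before the A and B probes are identified.
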